## Abstract

**Background:**

The worldwide concern about safety has created a need for new and effective strategies to improve safety in the workplace. Based on reported studies, approximately 90% of workplace accidents are due to unsafe behaviour and human error. Therefore, the most important strategy in reducing the rate of these accidents is training workers regarding safe behaviour and avoiding human error. There is limited research on understanding the barriers to promoting safe behaviour amongst petrochemical workers. This paper presents a protocol for an intervention study, using training sessions in combination with an educational software (application). The intervention aims to both promote workers’ safe behaviour and reduce the rate of occupational accidents.

**Methods:**

One hundred seventy-six workers will be recruited to this study from an Iranian petrochemical industry. The study is Mixed Methods Research (MMR) which will be carried out in two phases. In the first phase, using a qualitative approach, in-depth interviews will identify the causes of unsafe behaviour in the petrochemical industry. In the second phase, models of safe behaviour used in workplaces and the petrochemical industry will be investigated. The findings of the first phase will be matched with the constructs of these models to produce a well-suited conceptual model. Questionnaires and an educational intervention will be designed based on the results of the two phases. The workers will receive training interventions using direct methods, involving training sessions and workshops, and in an indirect method for which educational software will be designed. A randomised controlled trial (RCT) will assess comparability between the intervention group and the control group at baseline, after the intervention, and at a three-month follow up.

**Discussion:**

This research will provide a practical approach for promoting safe behaviours and reducing occupational hazards amongst industrial workers.

**Trial registration:**

Iranian Registry of Clinical Trials: IRCT20170515033981N2. Registered 19 June 2018.

## Background

Work-related accidents and injuries in industrial organisations have always been a major issue worldwide [1]. Despite all the positive changes and improvements in organisational structures and various technological developments in industrial settings, the number of serious injuries and occupational accidents has not decreased during the last decades [2, 3]. Moreover, as Sunindijo and Zou [4] argue, while the industry employs only about 7% of the workforce worldwide, it is responsible for 30–40% of fatalities. Based on statistics, 100,000 workers are killed on construction sites every year —one person every five minutes due to unsafe working conditions [5]. Annually, according to the International Labour Organization (ILO), it is estimated that more than 2.2 million workers die as a result of occupational accidents and work-related diseases. Across the globe, workers suffer approximately 270 million occupational accidents that lead to absences from work for three days or more, and fall victim to some 160 million incidents of work-related disease each year [6]. While cancers and cardiovascular diseases kill more workers than occupational injuries, the number of Years of Life Lost to work-related injuries is still significantly high as those injured were much younger than, for example, those who died from work-related cancers [7]. This fact highlights the importance of conducting research on safety in the industrial settings. Research in the area of occupational safety related to safe work behaviour has become prominent during the past decades [8]. Ensuring safe and healthy working conditions is an essential element of the quality of work life [9, 10]. Several researchers have attempted to determine the effects of workers’ occupational safe behaviour on work injuries across a range of industrial settings [11, 12]. Findings from a number of studies have indicated that unsafe work behaviour increases the probability of accidents and fatal injuries in organisations [13]. For example, Shin and colleagues [14] state that approximately 88% of workplace incidents in the construction industry are caused by unsafe behaviour, 10% by unsafe conditions and 2% by unforeseeable factors. Accordingly, all these reasons signify that safety has been considered an important issue in industrial settings. It is especially so in developing countries where workplace safety is a major area of concern because of the lack of safety regulations [15]. Therefore, identifying such unsafe acts and conditions is the first step in taking action to eliminate them, minimize the risk of work-related injuries or illnesses and prevent further accidents [16].

Behaviour-based safety (BBS) has been explored extensively across a variety of disciplines [13, 17–19]. Research focuses mainly on both person and situational aspects to explain safety in industrial environments and how individual and contextual factors interact to influence workplace safety [20]. The role of the construction project manager is crucial in increasing the level of safety performance [4]. Findings indicate that managers are responsible for the implementation of the safety policies of the company as well as the management of challenging tasks which require them to have sufficient skills [21]. Thus, managers need the ability to influence workers to adopt positive behavioural attitudes and intentions towards work safety [22]. They also should report and investigate work-related accidents and near-misses to identify the root causes, and receive feedback from worker [23, 24]. Safety climate culture is generally accepted as another crucial indicator for enhanced safety in organisations [25, 26]. A number of notable safety climate studies provide empirical evidence to support a positive link between safety climate and safe work behaviour [27–29]. Zohar defined safety climate as the sum of shared perceptions among employees with regard to safety procedures, policies, and practices in the work environment [30]. The development of a safety climate could be related to the elimination of unsafe acts and conditions and could lead to the prevention of occupational accidents and safety performance improvement [31, 32]. Another major contribution of the origins of safety performance is workers’ knowledge of the safety procedures to manage safety risks [33]. It is predicted that workers tend to make mistakes because they have lack of understanding on how to follow organisational safety procedures and regulations, are unaware of the potential hazards in their work environment, and have negative attitudes towards safety [34]. It is therefore expected that a higher level of knowledge acts as a mechanism that increases workers’ behavioural intentions to engage in safe work behaviours [35, 36].

Based on the published data from Iran, the trend of occupational accidents and work-related diseases is the same as the rest of the world [37]. According to the Iranian Ministry of Labour, work-related injuries are mainly caused by unsafe work conditions as well as some individual characteristics [38]. Petrochemical industries have been classified as a high-risk industry to the potential for serious occupational accident consequences and severe effects to the environment [39]. Iran exports its petrochemical products to several dozen countries in different parts of the world and this has positioned Iran as the second largest producer and exporter of petrochemicals in the Middle East [40]. Norozi and colleagues reported that in Iranian petrochemical companies, more than 198 fatal injuries occurred over the last decade [41].

Research has shown that training of workers plays the most vital role in safety at work [42]. There is evidence that safety training is considered as a safety improvement intervention to reduce accident rates [43]. First aid training and safety training is the enhancement of safety knowledge that should be known by workers to guide them in how to improve their compliance with health and safety requirements. Managers must provide direct safety practices for workers to understand safety procedures [43, 44]. The importance of safety training has also been emphasised by Loosemore and Malouf [45] who found that the knowledge acquired through many training programs often made workers more aware that their own behaviour and was an important factor in the avoidance of work-related injuries and illnesses, and also appeared to reduce workers’ willingness to accept prevailing levels of occupational safety risk on industrial sites.

By considering the increasing number of recent accidents in Iranian petrochemical companies, qualitative research enables us to more fully understand workers’ perceptions of the factors influencing safe behaviour and how to promote and maintain such behaviour which will, in turn, prevent injuries and workplace absenteeism. This paper presents the design of a study for the educational intervention in an Iranian petrochemical company, in which multiple forms of data (qualitative and quantitative) are incorporated and evaluates the intervention’s effectiveness. We hypothesize that this intervention will be effective in terms of promoting safe work behaviour and will also reduce work-related incidents in the intervention group at the end of the study, compared to the control non-intervention group.

### Aims and research question

The overall aim of this study is to design and evaluate an educational intervention to promote workers’ safe work behaviour. The specific objectives include:To design/ develop a conceptual model of safe work behaviour based on qualitative data;To design/ develop a questionnaire of safe behaviour based on the constructs of the conceptual model;To design an educational intervention based on the findings of the first two phases of the study to promote and maintain safe work behaviour.

The main research question is to determine whether the educational intervention leads to the promotion and maintenance of safe behaviour in the intervention group compared to the control group.

## Methods

This study will be conducted and reported on the basis of Consolidated Standards of Reporting Trials (CONSORT) 2010 statement [46].

### Study design

The educational intervention will be evaluated using a randomised controlled trial. The Medical Research Ethics Committee of Tarbiat Modares University in Iran approved the study protocol (Approval ID: IR.TMU.REC.1395.503). All participants will provide written consent to participate in the study, will be advised that data are going to be anonymised, securely stored, and analysed for publication. They will be advised that participation will be voluntary, and they are free to leave the study at any time. A flow diagram of randomized controlled protocol is shown in Fig. 1.

**Fig. 1 Fig1:**
[figure not shown]
CONSORT flow diagram of the study design. This study will be conducted and reported on the basis of Consolidated Standards of Reporting Trials (CONSORT) 2010 statement. The figure shows the flow diagram of randomized controlled protocol

### Study sample

#### Participant recruitment and eligibility criteria

A total of 176 workers will be recruited from an Iranian petrochemical industry. Since we seek to obtain a broad cross-section of worker opinions and experiences, we will use a combination of purposive sampling and maximum variation sampling strategies. Staff from the company’s Safety, Health and Environment unit, who are not part of the research team, will invite workers, supervisors, and safety managers from various occupational groups working in the operations department and the maintenance and repair department who have experienced accidents and injuries or have witnessed colleagues’ accidents to participate in the study (purposive sampling). Workers are eligible to participate if they have (1) work experience in the petrochemical industry for at least two years, and (2) participants’ motivation to recount their experiences to the researcher. The exclusion criteria include (1) the reluctance of participants to continue to participate in the study, and (2) the lack of regular attendance at training sessions. During the interviews, respondents will identify employees who have information about workplace accidents in the company and are key informants (snowball sampling). These employees will also be invited to participate in the study. Before the start of each interview, a member of the safety staff will introduce the participant to the first author, who will provide clear verbal information about the study.

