#### Setting and sample size

The research setting is a petrochemical industry in Iran. The study population consists of workers of this Iranian petrochemical company. Since this study aims to promote workers’ safe behaviour, as reported by Waters and Duncan [47] (a similar study), the effect of the behavioural safety program interventions that is considered as the dependent variable in this study has been 40%, if it is assumed that environmental factors and non-compliance by control group participants account for about 50% of this effect, namely 20%, for each group, based on the following formula [48] and with 95% confidence interval and 80% power of a test, 78 participants will be required.. The researcher will hypothesize a 10% attrition rate (in both groups). In order to ensure that the total sample size is available, the researcher will need to recruit more participants to allow for attrition. Therefore, with the anticipated attrition rate, the researcher should enrol 176 participants. The participants will be randomly allocated to the intervention group (*n* = 88) or the control group (*n* = 88).$$ {\displaystyle \begin{array}{c}n=\frac{{\left({Z}_{1-\alpha 2}+{Z}_{1-\beta}\right)}^2\left({P}_1\left(1-{P}_1\right)+{P}_2\left(1-{P}_2\right)\right)}{{\left({P}_1-{P}_2\right)}^2}\\ {}=\frac{{\left(1.96+0.84\right)}^2\left(0.4(0.6)+(0.2)(0.8)\right)}{{\left(0.4-0.2\right)}^2}=78.4\end{array}} $$

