#### Questionnaires

The questionnaire will consist of two parts. The first part will cover social demographics and the second part will include the constructs of the conceptual model. Data will be collected at baseline, after the intervention, and after three months for workers from the intervention group and the control group. The questionnaires will be anonymous to promote participation and workers’ confidence in the intervention. All the participants who will be doing measurements will be blinded to the assigned groups of the study.

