#### Intervention

The intervention will include multiple components associated with information obtained from pre-test stage and constructs of the conceptual model. Participants will attend eight weeks of biweekly 90-min intervention sessions. Each session will consist of two parts, a 60-min interactive workshop followed by a 30-min group activity. There will be different themes for each of the workshops, which will start with a presentation to highlight the important factors, and effective strategies for changing unsafe behaviour to overcome barriers they may have encountered and discussions between workers and the researcher. Then, each workshop will be followed by group activities. All video and written teaching materials for these sessions will be prepared by the research team. One important goal of the workshops is to teach workers how to identify workplace hazards, to promote their own safe behaviour and maintain it. In the second part of the intervention, texts and messages related to different aspects of workplace safety will be sent to the participants in the intervention group via WhatsApp. Apart from the workshops, there will be two consultation sessions with managers and supervisors during the intervention period. These sessions will prompt them to be fully committed to safety issues so that top prioritisation of safety will be widely accepted. Finally, educational software (multimedia) will be designed. Participants allocated to the control group will be asked to attend measurement sessions, but they will only receive the intervention six months later (i.e., after the follow-up time point).

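### Irregular training attendance is an exclusion criterion that arises after randomisation and that only the intervention arm can fail, which opens the group comparison to selection bias if excluded workers leave follow-up or analysis

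*Protocol article*

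**What the plan says.** Under *Participant recruitment and eligibility criteria*, the protocol article gives two exclusion criteria: "1) the reluctance of participants to continue to participate in the study" and "2) the lack of regular attendance at training sessions". It sets no threshold for regular attendance.

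The only training described is the trial intervention. In the *Intervention* section, "Participants will attend eight weeks of biweekly 90-min intervention sessions". The same section has controls come in for measurement alone during this time and says of their own training: "they will only receive the intervention six months later (i.e., after the follow-up time point".

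Under *Questionnaires*, outcomes are collected in both groups at baseline, after the intervention and three months later. The analysis paragraph at the end of the *Intervention* section measures effectiveness by the difference between the study groups. *Setting and sample size* plans on 40% versus 20%, randomises 88 per arm and makes one allowance for loss: "The researcher will hypothesize a 10% attrition rate (in both groups").

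**The concern.** An eligibility rule should depend on what is known before allocation. This one depends on behaviour under the allocated treatment, and one arm has no opportunity to show that behaviour before the last outcome is measured. Applied as written, the rule removes the less engaged workers from the intervention arm and leaves their counterparts among the controls.

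The section *Phase three: randomised controlled trial (RCT)* justifies the design by its freedom from confounding and selection bias. A one-sided exclusion after randomisation gives that up. Workers who miss safety training may well be those who behave less safely. In that case the remaining intervention arm would look better than the controls even if the training did nothing. With no definition of regular attendance, the decision on whom to exclude is also left open until after allocation.

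**Working it through.** **1. Who can fail the criterion, and when**

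| Step | Where it stands | Consequence |
|---|---|---|
| Irregular attendance excludes | Participant recruitment and eligibility criteria | Needs attendance data |
| Training is the trial intervention, given over eight weeks | Intervention | Attendance is known only after allocation |
| Controls attend measurement sessions only, and are trained after follow-up | Intervention | No control can fail before the last outcome |
| The last outcome is at three months, in both groups | Questionnaires | The exclusion precedes the outcome in one arm only |

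**2. The plan's own sample size**

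(1.96 + 0.84)² × (0.4×0.6 + 0.2×0.8) / 0.2² = 7.84 × 0.40 / 0.04 = 78.4 per arm. Allowing for 10% attrition, 78.4 / 0.9 = 87.1, rounded up to 88 per arm and 176 in total. The stated figures reproduce and are not in question.

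**3. Illustrative size of the selection effect**

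From the article: a control rate of 20%, 88 per arm and two-sided 5%. Assumed, because the article gives no figures: no true effect, a share *e* of the intervention arm excluded, and a safe-behaviour rate *r* among those excluded.

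The rate in the remaining intervention arm is p = (0.20 − e·r) / (1 − e), and the spurious difference is d = p − 0.20. With n₁ = 88(1 − e) and n₂ = 88, the type I error is the probability that a two-proportion z-test (pooled standard error SE₀ under the null, unpooled SE₁ otherwise) rejects in either direction:

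P(reject) = Φ((d − 1.96·SE₀)/SE₁) + Φ((−d − 1.96·SE₀)/SE₁)

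| e | r | n₁ | p | d (points) | Type I error |
|---|---|---|---|---|---|
| 10% | 0% | 79.2 | 0.20/0.90 = 22.2% | +2.2 | 6.5% |
| 10% | 15% | 79.2 | 0.185/0.90 = 20.6% | +0.6 | 5.1% |
| 20% | 0% | 70.4 | 0.20/0.80 = 25.0% | +5.0 | 11.9% |
| 20% | 15% | 70.4 | 0.17/0.80 = 21.25% | +1.3 | 5.5% |

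Worked line for e = 20%, r = 0: SE₀ = 0.0665 and SE₁ = 0.0669, so the upper tail is 0.115 and the lower tail 0.0035, 0.119 in total. If r = 20%, so that attendance is unrelated to the outcome, then d = 0 and the bias vanishes.

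**4. What keeping everyone does to power**

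Assume that attenders respond at 40% and non-attenders at the control rate of 20%, with 88 analysed per arm. The intervention rate is then 0.40(1 − e) + 0.20e.

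| Non-attendance | Intervention rate | Power (pooled z-test) |
|---|---|---|
| 0% | 40% | 83% |
| 10% | 38% | 75% |
| 20% | 36% | 66% |

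**The case against.** The article does not say in so many words that excluded workers go unmeasured or are left out of the analysis. The section mixes recruitment for the interviews with recruitment for the trial. The article is condensed, commits to CONSORT 2010, and may have an analysis plan that defines an all-randomised set. This stands to the extent that the bias must be stated conditionally. It does not remove the point, because the fault is a rule that is written down rather than something left out. Training sessions can only mean the trial intervention, and an all-randomised analysis set elsewhere would contradict the criterion as it reads.

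A reader might infer more than the document supports:

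- **That both exclusion criteria share the fault.** Reluctance to continue is withdrawal. Either arm can exercise it, and *Study design* guarantees the freedom to leave. Only the attendance criterion is one-sided.
- **That these exclusions come on top of the 10% attrition.** Attrition is not defined in *Setting and sample size*, so irregular attenders may already be counted in it.
- **That power lost through exclusion is a further argument against the plan.** Keeping non-attenders also lowers power through dilution, so power does not favour the change.
- **That the bias is of known size and direction.** No attendance rate, and no outcome rate by attendance, is given.

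**Conclusion.** The point holds in a limited form. As written, the attendance criterion operates after randomisation and can exclude only intervention-arm workers; that follows directly from the text. If exclusion means leaving follow-up or analysis, the comparison is open to selection bias, in favour of the intervention if irregular attenders behave less safely.

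The magnitude is illustrative only. Under the assumptions shown, it runs from negligible (+0.6 points, type I error 5.1%) to material (+5.0 points, about 12%, against a planned difference of 20 points). Confidence is high that the criterion is one-sided, but not about how large the bias would be. The article does not support the flat statement that the analysed groups will no longer be the randomised ones.

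**What to change.** - Remove attendance from the exclusion criteria.
- State that every randomised worker is invited to all measurement sessions regardless of attendance, and that all randomised workers are analysed in their allocated group.
- Define regular attendance and record it as an adherence variable, used only in a secondary per-protocol or complier-average analysis.
- Restate reluctance to continue as voluntary withdrawal, open to either arm, with data already collected kept where consent allows.
- Describe the stated 80% power as assuming full attendance.

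The cost is more than wording. Non-attenders have to be followed up, and keeping them dilutes the effect. With 20% non-attendance and those workers responding at the control rate, the intervention rate falls from 40% to 36% and power to about 66% with 88 per arm.
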